## Abstract

**Background:**

Headache is one of the most common pain symptoms in childhood having a negative impact on many aspects of the lives of affected children, both short-term and long-term. Therefore, it is important to document safe and effective treatment options. Chiropractic spinal manipulation is a commonly used treatment option for these patients, although there are no randomized clinical trials documenting the effectiveness of this in pediatric headache. However, there is moderate evidence for effectiveness of spinal manipulation for adults with tension-type and cervicogenic headaches.

This paper describes the protocol for a two-armed randomized superiority clinical trial aiming to investigate the effectiveness of chiropractic manipulation versus sham manipulation in the treatment of recurrent headache in children aged 7–14.

**Methods:**

Children with weekly headaches for at least six months will be included if they have indications for chiropractic manipulation. The participants will be randomized to either chiropractic manipulation or sham manipulation. Both children and parents will be blinded for allocation. There will be 100 children in each arm and they will answer weekly text messages four weeks prior to treatment and during a four months treatment period. Potential primary outcomes are weekly number of headaches, intensity of headache, medication use and global perceived effect. Secondary outcomes include side-effects and headache status after one year.

An initial outcome data analysis will be performed to inform the choice of primary outcome (adaptive design). Intervention effects will be reported as the difference in mean values between the two treatment arms, Cohen’s effect size and numbers needed to treat.

**Discussion:**

A major strength of this study is its pragmatic nature, where the active treatment group receives chiropractic manipulation according to their individual needs, while both groups continue their use of medication for headache according to their pre-trial habits. Other strengths include an elaborate sham procedure and the weekly outcome reports, reducing recall bias.

If it is possible to develop effective treatment for headache in children, a life course of recurring problems may be altered with potential positive implications for both individuals and society.

**Trial registration:**

ClinicalTrials.gov, identifier NCT02684916.

**Electronic supplementary material:**

The online version of this article (10.1186/s12998-019-0262-y) contains supplementary material, which is available to authorized users.

## Background

Headache is one of the most common pain symptoms in childhood and experienced by up to 80% of 13–15 year old children [1]. Besides the pain and emotional distress, children with recurrent headaches have reduced participation in social activities [2] as well as more school absenteeism and lower academic performance when compared to children without recurrent headache [3]. Socioeconomically disadvantaged children are more prone to headaches [4, 5] and children with headaches generally have poorer overall physical health with higher frequency of asthma, hay fever, anemia, stomach and intestinal illness, obesity and ear infections. Furthermore, they have a higher prevalence of learning disability and attention deficit disorders when compared to children without headaches [5]. Importantly, pediatric headache can be a precursor to potentially severe headache syndromes later in life [6–8].

The etiology of pediatric headache is multifactorial and complex and several causative factors have been proposed, including family history of headache [3], headache medication overuse [9], sleep disturbances [10], depressive/anxious traits [3], stressors [9], a higher rate of divorced parents, fewer peer relations and an unhappy family atmosphere [11]. Headache can also be the result of trauma to the head and neck [12, 13], and in children below the age of six with recurrent and chronic headaches, post traumatic headache is the most frequent type of secondary headache [14]. Headache after minor head, neck or back injury often displays the same symptoms as other types of chronic tension type headache or migraine but they typically have a history of recurrences, and it has been suggested that symptoms may be delayed for months or even years after the injury [15–17]. Finally, prolonged static postures, especially prolonged reading and computeruse, has been associated with headache in 10–13-year-old children [18]. Both trauma and non-appropriate strain of the neck may lead to mechanical problems of the cervical spine. According to the American Migraine Foundation, cervicogenic headache is referred pain perceived in the head from a source in the neck. Cervicogenic headache is a secondary headache, caused by a disorder of the cervical spine and its components: bone, disc and/or soft tissue elements. Numerous pain-sensitive structures exist in the cervical and occipital regions. The junction of the skull and cervical vertebrae have regions that are pain generating, including the lining of the cervical spine, the joints, ligaments, cervical nerve roots and vertebral arteries passing through the cervical vertebral bodies [19]. Therefore, spinal manipulative therapy has been suggested as a treatment option for these headaches [20].Pharmacologic treatment is commonly used in pediatric headaches despite very few randomized controlled trials documenting its effectiveness [7, 21]. Spinal manipulation, spinal mobilization and massage are also used, and in Denmark headache is the second most common complaint among children aged 2 to 17 years old seeking chiropractic treatment [22]. While there are no randomized clinical trials documenting the effectiveness of chiropractic manipulation in pediatric headache [23], there is moderate evidence for effectiveness of spinal manipulation for adults with cervicogenic headache [24] as well as for tension-type headache [25]. Serious adverse events following chiropractic manipulation appear to be very rare [26] and the relative risk of having a minor or moderate adverse event after high velocity thrust spinal manipulation was significantly less than after taking medication which is often prescribed for painful conditions [27]. In a review of compensation claims following chiropractic treatment in Denmark and Norway between 2004 and 2012, there were no reports of harm or injury resulting in compensation claims in children age 0–18 years old [28].

In this paper, we describe the protocol for a two-armed randomized superiority clinical trial aiming to investigate the effectiveness of chiropractic manipulation versus sham manipulation in the treatment of recurrent headache in children aged 7–14. Both groups receive oral and written lifestyle advice that is beneficial to headache patients, and they can use medication according to individual needs throughout the trial. Consequently, our design allows us to investigate the specific effect of chiropractic manipulation on top of standard care.

## Method

### Procedures

#### Recruitment

The recruitment for this trial began November 2015, by January 2nd 2019, 180 children were included and recruitment is expected to be concluded by June 2019. School principals in the region of Northern Jutland, Denmark, are contacted by telephone and asked for permission to distribute an invitation (Additional file 1) to all 1st -7th grade children through the Danish School Information Network, which is the official communication line between the school, the child and the parents. Furthermore, information is distributed through local newspapers, television and radio, as well as social media. Parents with children aged 7–14 suffering from recurrent headaches are invited to contact the project clinic for screening for inclusion in the trial.

#### Setting and pre-randomization procedure

The project clinic is a primary care chiropractic practice owned by the primary investigator. Upon contact, thorough information about the study is given by a project secretary on the telephone, including information about the two treatment arms and blinding procedures. If the parents decide to participate, the secretary will check inclusion/exclusion criteria (see Table 1) and send them written information as well as an informed consent form, including a pre-stamped return envelope. Within a week, the consent form, signed by a parent/guardian, should be sent to the Nordic Institute of Chiropractic and Clinical Biomechanics (NIKKB), where a research assistant and data manager will contact the parents by telephone and initiate a four-week pre-treatment observation period. During this period, the parents and the child together answer the following three questions every Sunday, sent to the parents as a text message (SMS) on their cell phone:“How many days has <child’s name> had a headache this week? Choose a number between 0 and 7.”“How will you rate the pain on a scale from 0-10, where 0 is no pain and 10 is the worst pain you can imagine?”“How many pills for headache has < child’s name> taken this week? 0: none, 1: 1-4, 2: more than 4 pills.”

**Table 1 Tab1:** Inclusion and exclusion criteria with their respective time points

Inclusion criteria	Time point for checking*
7–14 years old	1
at least one episode of headache per week for at least half a year prior to the pre-treatment period	2
At least one musculoskeletal dysfunction identified by the primary investigator as a movement restriction in one or more of the joints suitable for chiropractic manipulation treatment at the time of the initial screening.	3
written informed consent from the holder(s) of custody	1
a mobile telephone in the family and ability to report weekly headache data	1
ability to read and speak Danish at an adequate level to comply with study requirements	2
*Exclusion criteria*	
contraindications for joint manipulation (Additional file 3)	3
receiving any treatment by a health care professional for headache within the last three months. The only exception being prescription pain medication	2
failure to report baseline data during four weeks prior to randomization	2

*Time points for checking inclusion and exclusion criteria: 1 = prior to start of four weeks pretreatment period; 2 = prior to screening visit; 3 = at screening visit

Before the start of the SMS-track, parents are contacted by telephone by a research assistant at NIKKB, instructing them to report the average of severity of all headaches during the previous week to the second question. Parents answer using the reply function, and the answers are automatically registered and stored in a database. If they do not reply, they will automatically get a SMS reminder the following Tuesday. The SMS-system is an efficient way to obtain frequent information and has been proven feasible, also in this age group [29]. Upon initiating this procedure, the data manager at NIKKB also sends an email to the parents containing a link to an electronic questionnaire through Survey Exact (https://www.surveyxact.com/) inquiring about the characteristics of the child’s headache problem, lifestyle, previous trauma, previous treatment, family history of headache and general health (Additional file 2). After the four-week pre-treatment observation period, the child and parents are scheduled for a screening at the chiropractor’s office after checking further inclusion/exclusion criteria (see Table 1).

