#### Outcome data

Throughout the study period, parents and participants answer the same weekly text messages on their mobile telephone as during the pre-treatment observation period, independent of the chiropractor.

At the end of the 4 months of treatment, all participating families receive a final text message including three questions:“How satisfied is <child’s name> with participation in this trial on a scale from 0-10, where 0 is the worst and 10 is the best you can imagine?”“How has the headache changed since <child’s name> started the treatment at the chiropractor? 1. almost gone/disappeared. 2. much better. 3. a little better. 4. same. 5. a little worse. 6. much worse. 7. worse than ever.”“In this trial there have been two groups. Do you think that <child’s name< was in group 1, who had standard chiropractic treatment or in group 2, that DID NOT have standard chiropractic treatment (please answer 1 or 2)?”

All participating families receive a questionnaire 1 year after entering the trial, including questions about headache status of the child as well as other treatments received for headache (Additional file 9).

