### Variables

#### Primary outcomes

*For each week we will consider three variables based on the weekly SMS:*
Number of days with headache per weekHeadache intensity on a pain scale from 0 to 10 per weekNumber of headache pills per week

To catch the effect of the intervention, we will consider the average values during the pre-treatment period and the final 4 weeks of the study period (week 14–17). Three primary outcomes are then given by the change over time, i.e. the difference between the average values from the final 4 weeks and from the pre-treatment period. The primary outcomes are prioritized as listed above. A fourth primary outcome is the global perceived effect (GPE) after 4 months based on the final SMS.

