The initial outcome data analysis will be performed by an independent statistician, who will obtain a copy of the data set with baseline characteristics, the weekly results for the three SMS questions and the GPE of the first 100 children. No information on treatment group membership will be provided. The statistician will prepare a statistical report to be distributed among the research team. The research team and the statistician will discuss the results and prepare a further short report summarizing the insights gained and potentially deciding on a reprioritization. We do not use a priori defined criteria for the decision to change the prioritization. In general, many different properties may pop up which may influence the decision. Consequently, it is hard to pre-specify an algorithm. Initial outcome analyses have rarely been performed until now, so there is no established framework for this. However, the decision will be based on a combination of the statistical findings and theory. We will therefore report the entire process for clarity (statistical report as well as a transparent report of the decision process). All analyses will be blinded and we can therefore exclude any undue influence on the final results of the study. Both reports will be finished prior to randomizing the last child in the study and will be included in the supplementary material of the first research publication.

In the primary analyses, we will visualize and describe the distribution of the four primary outcomes in each treatment arm. Intervention effects will be assessed by considering the difference in mean values between the two treatment arms, reported together with 95% confidence intervals and *p*-values. In addition, Cohen’s effect size defined as the difference in mean values divided by the common standard deviation will be reported.

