Multiplicity due to using four primary outcomes will be taken into account by applying the fixed sequence test principle [34] using the prioritization determined in the initial outcome analysis as the a-priori order of hypotheses. For all four primary outcomes, inference will be based on a least squares regression model. For each change score the baseline level will enter as covariate, and for the global perceived effect the number of days with headache per week will enter the model. In case the initial outcome analysis points to correlations between patient characteristics and outcomes above 0.3, these patient characteristics will be added as additional covariates. A responder analysis will be performed, reporting the proportion in each group reporting 20, 25, 50 and 75% improvement compared to baseline for the three change scores. Furthermore, numbers needed to treat, with success defined as 20% improvement, will be estimated.

Secondary outcomes will be analyzed similarly.

Patient and treatment characteristics as well as drop out frequencies and patterns will be described within each treatment group. Single missing values in the SMS data will be ignored, as long as there is at least one value available within the last 4-weeks periods. Patients with missing answers to all 4 weeks in last period will be ignored (complete case analysis). Missing values in baseline characteristic will be replaced by regression-based predictions from the other baseline variables, using least squares regression to predict continuous variables, and ordinary, ordinal or multivariate logistic regression for binary, ordinal and categorical variables.

Multiple imputation will be used to conduct sensitivity analyses with respect to handling missing values. These will be based on a chained equation approach (as implemented in Stata’s mi command) considering simultaneously all outcomes and baseline variables. Analyses of data will be conducted by a researcher, otherwise not involved in the project and who will be blind for the group coding. The clinical investigators will not be involved in the analyses.

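### The weekly pill item yields only a three-level code, so labelling it a pill count and applying percent-improvement responder thresholds to it is wrong as written

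*Protocol article*

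**What the plan says.** All references are to the protocol article.

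- **Collection.** Under Setting and pre-randomization procedure, the third weekly SMS question asks for pills "taken this week? 0: none, 1: 1-4, 2: more than 4 pills". Under Outcome data, families "answer the same weekly text messages on their mobile telephone as during the pre-treatment observation period", so no finer count is obtained later.
- **Definition.** Primary outcomes lists the variable under a name that denotes a weekly count of pills. The outcome is "the difference between the average values from the final 4 weeks and from the pre-treatment period". Pills stand third in the listed priority.
- **Analysis.** Under Statistical analyses, "Intervention effects will be assessed by considering the difference in mean values between the two treatment arms", with Cohen's effect size in addition. "For all four primary outcomes, inference will be based on a least squares regression model", and "For each change score the baseline level will enter as covariate".
- **Responders.** The same section reports the proportion in each group "reporting 20, 25, 50 and 75% improvement compared to baseline for the three change scores". Pills are one of the three and are not exempted. A number needed to treat at 20% improvement follows, without naming the outcome or outcomes it covers.

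The article nowhere assigns pill values to the codes or describes the pill result as a category score.

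**The concern.** The codes 0, 1 and 2 stand for none, a range of 1 to 4, and an open-ended range from 5 upward. The steps are unequal in pills and the top has no limit. A mean of such codes is a score, and a difference in means is a difference in score. Read under the present label, it would be taken as pills per week, which were not measured.

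The percent-improvement rule is the more serious part. A percentage needs a scale with a true zero and equal units. On this code, the same proportional fall in pills can score nothing or a great deal, depending on whether it crosses a category boundary. The ratio also has no value when the baseline mean is zero. The plan would therefore publish responder proportions at four thresholds for a declared primary outcome that do not mean what their label says.

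**Working it through.** The plan states no power, effect size or distribution for the pill outcome, so there is no figure to reproduce. The check applies the plan's own rules to example weekly counts. The counts are illustrative assumptions.

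**Rules used.** Code = 0 for 0 pills, 1 for 1 to 4, 2 for 5 or more. Average over four weeks before treatment and over weeks 14–17. Percent improvement = 100 × (baseline mean − final mean) / baseline mean, computed once on pills and once on the code.

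| Weekly pills before | Weekly pills after | Mean pills | Improvement in pills | Mean code | Improvement on code |
|---|---|---|---|---|---|
| 4,4,4,4 | 1,1,1,1 | 4 to 1 | 75% | 1 to 1 | 0% |
| 20,20,20,20 | 5,5,5,5 | 20 to 5 | 75% | 2 to 2 | 0% |
| 12,12,12,12 | 5,5,5,5 | 12 to 5 | 58.3% | 2 to 2 | 0% |
| 5,5,5,5 | 4,4,4,4 | 5 to 4 | 20% | 2 to 1 | 50% |
| 5,4,5,4 | 4,4,4,4 | 4.5 to 4 | 11.1% | 1.5 to 1 | 33.3% |
| 4,4,4,4 | 1,1,1,5 | 4 to 2 | 50% | 1 to 1.25 | −25% |
| 0,0,0,0 | any | 0 at baseline | undefined | 0 at baseline | undefined |

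- **Missed responders.** Rows 1 to 3 are large reductions that fail every threshold.
- **Inflated response.** Row 4 meets only the 20% threshold on pills but meets 20, 25 and 50% on the code. Row 5 meets none on pills but meets 20 and 25% on the code.
- **Reversed sign.** In row 6 total pills halve (16 to 8), while the code sum rises from 4 to 5.

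**Constant-use grid.** Take baseline 1 to 10 and final 0 to 10 pills per week, which gives 10 × 11 = 110 pairs. Pairs with a true reduction of at least 20%, by baseline value 1 to 10, number 1+2+3+4+5+5+6+7+8+9 = 50. Of these, 16 are not 20% responders on the code: 6 stay within the 1–4 category and 10 within the top category. No pair is a responder on the code without being one on pills. This shows the direction of error under constant use. It is not an estimate of frequency in the trial.

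**Granularity.** The four-week mean code has nine possible values (0, 0.25, …, 2). With a baseline mean of 1.0, the only possible results short of worsening are 0, 25, 50, 75 and 100%, so the 20% and 25% thresholds coincide. With a baseline mean of 0.25 they are 0 or 100%.

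**Zero baseline.** Table 1 requires at least weekly headache and sets no requirement for medication use, so a child coded 0 in all four run-in weeks can enter. Such a child has no defined percent improvement.

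**The case against.** Four arguments on the other side deserve weight.

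1. *Least squares on ordered scores is legitimate.* This stands. With 1:1 randomisation and about 100 children per arm, a baseline-adjusted comparison of mean scores is a valid test of a score shift. A reader might infer that the confirmatory test of the pill outcome is invalid, or that an ordinal model is required. The article does not support that. An ordinal model would not recover the reductions in rows 1 to 3 either, because the item itself does not record them.
2. *The number needed to treat is not tied to pills.* This also stands. A reader might infer that one will be computed from the pill code, but the sentence names no outcome. The most that can be said is that the wording does not exclude it.
3. *The blinded initial outcome analysis may deal with it.* Only in part. That analysis examines floor and ceiling effects, informs the choice between absolute and relative change, and may reorder the outcomes. It does not change the item, the label or the responder rule. If it chose relative change, the pill outcome itself would become undefined at zero baseline. The Discussion's remarks on medication reporting concern who knows what was taken, not the scale.
4. *The examples are hypothetical, and some cases agree.* True. A fall from 1 pill to 0 is 100% on both scales, and 5 to 4 meets the 20% threshold on both. The rule is still unsound at the other thresholds and with use that varies by week.

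Handling of children with zero baseline could by itself be left to an analysis plan that is not shown. The percent rule for pills could not, because the article states it.

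**Conclusion.** The point holds for the label and for the percent-improvement use of the code, which are wrong as written. Percent change on this code can be 0% for a true 75% reduction, 50% for a true 20% reduction, and of the wrong sign where use varies by week. It is undefined for children with no pills throughout the run-in.

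Severity is moderate. Pills are third in the initial fixed sequence, the sample size rests on headache days, and the test of the mean score is sound as a test of a score. The conclusion rests on the item being used unchanged throughout, as Outcome data says. The number of children misclassified or left undefined cannot be estimated from the article.

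**What to change.** Leave the SMS question as it is. Then:

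- Rename the outcome *weekly headache-pill category score (none / 1–4 / >4)*, and state that any mean difference is in score units, not pills.
- Remove pills from the 20/25/50/75% responder analysis, from any relative-change version of the outcome, and from any number needed to treat. State which outcomes the number needed to treat covers.
- If a responder figure for medication is wanted, make it category-based. One option is the proportion whose mean category fell from baseline, among children with some baseline use (a subset defined before randomisation). Another is the proportion with no pills in weeks 14–17, adjusted for baseline use so that children who took none at the start are not simply counted as successes.
- Keep the baseline-adjusted least squares analysis of the mean score as the test. An ordinal model may be added as an optional sensitivity analysis.

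The cost is a change of wording and one table. Data already collected (180 children included by January 2019) are unaffected. The blinded reports due before the last child is randomised are a natural place to record the change. The price is that the pill result can no longer be expressed in pills or percent. The relabelling does not restore information that the coarse item never captured.
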